# OBJECTIVES

## Primary objectives

To examine the effects of equivalent weight loss with and without exercise on breast cancer biomarkers (endogenous sex hormones) in overweight, sedentary postmenopausal women.

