## Diet-induced weight loss intervention (group D)

Women randomised to diet only group will be prescribed a diet creating a mean energy deficit of 500 kcal/day during a weight reduction period of 10-14 weeks. This is assumed to produce a weight loss of 5-6 kg in total (approximately 0.5 kg per week). Diet composition and recommendations will be comparable to the baseline diet.

The weight reduction period, will be followed by a weight maintenance period of 2-6 weeks in which energy intake and energy expenditure will be balanced. The weight maintenance period starts as soon as the individual weight reduction goal is obtained (total weight loss of 5-6 kg), or in study week 19. From this time point until end of study, energy intake should meet the individual energy requirements for weight maintenance.

*Dietary counselling during the weight reduction intervention phase (see fig 1) will consist of:*

- Two individual 30 minutes individual sessions with a dietician. During the first session (week 6), individualised instructions are given on how to create the daily energy deficit of 500 kcal and perceived individual pitfalls will be discussed. The second session will take place at the end of the weight reduction phase in order to instruct the participant on how to maintain the reduced body weight.
- Five group sessions: In these one-hour sessions, participants in this treatment arm will be trained for self-management of body weight reduction and maintenance at the long run.
- Seven phone calls: the dietician will contact the participants by phone to evaluate body weight, motivate them and discuss diet adaptations if necessary.
- Completion of a food-record once during the intervention period. Participants will be instructed by the dietitian to record their daily food intake using a food-diary for 3 consecutive days (2 weekdays and 1 weekend day) De dietitian will provide feedback on energy and nutrient content of the reported intake

*Background principles and structure of the weight loss intervention:*

We use several theoretical models53-55 putting different emphasis on the key psychological processes of behavioral change. In accordance with these models, the following methods56-59 will be used to modify woman’s behavior depending on her individual characteristics and preferences:

- Self-monitoring of body weight and energy intake

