| **Warming-up** | 5-10 | 60-65% | | 60-65% | | 60-65% | |
| **Endurance training** | 20-25 | 60-70% | | 70-80%  (5-10 min 80-90%) | | 70-90%  (high-intensity interval training; see table 2) | |
| **Strength exercises** | 25 | Increasing intensity and decreasing number of repetitions (see  Table 3a-b) | | | | | |
| **Cooling down** | 5 |  |  | |  | |  |

Table 2. High intensity endurance interval training during phase 3

| **Week** | Intensity | **Repetitions** |
| --- | --- | --- |
| 9 | 70% | 10 |
| 10 | 75% | 10 |
| 11 | 80% | 10 |
| 12 | 80% | 15 |
| 13 | 85% | 15 |
| 14 | 90% | 15 |

Table 3a. Strength exercises week 2-8

| **Muscle Group** | Exercise | **Intensity** |
| --- | --- | --- |
| Back | Rowing | 1x 20-25 reps |
| Chest | Bench press | 1x 20-25 reps |
| Legs (hips, glutes and thighs) | Squat | 1x 20-25 reps |
| Shoulder | Shoulder press | 1x 20-25 reps |
| Arms (biceps) | Bicepscurl | 1x 20-25 reps |
| Legs (hips, glutes and thighs) | Lunges | 1x 20-25 reps |
| Legs (calfs) | Calf-raises | 1x 20-25 reps |
| Arms (triceps) | Triceps extension | 1x 20-25 reps |
| Abdominal | Crunch | 1x 30-40 reps |

Table 3b. Strength exercises week 9-14

| **Muscle Group** | Exercise | **Intensity** |
| --- | --- | --- |
| Back | Rowing | 2x 15-20 reps |
| Chest | Bench press | 2x 15-20 reps |
| Legs (hips, glutes and thighs) | Squat | 2x 20-25 reps |
| Shoulder | Shoulder press | 2x 10-15 reps |
| Arms (biceps) | Bicepscurl | 2x 20-25 reps |
| Arms (triceps) | Triceps extension | 2x 20-25 reps |
| Abdominal | Crunch Hoover | 2x 30-50 reps |

The energy requirements of a group exercise session is based on the compendium of physical activities of Ainsworth et al71, 72.

In this compendium average metabolic equivalent (MET) rates are given. Since we have a specific study group of overweight and obese, sedentary postmenopausal women we calculated energy expenditure with the help of corrected MET’s specific for this population. Corrected MET’s can be calculated with the use of the Harris-Benedict formula.73, 74

We calculated a correction factor of 1.376

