Based on the baseline characteristics of our former conducted comparable study75 with a subanalysis of women with a BMI >25 kg/m2 , for the SHAPE-2 study we assumed an average weight of 78 kg, length of 1.65 m and age of 58 years. This gives us a correction factor 1.376 for the standard METs resulting in MET rates of 11 METs for the aerobic training (8*1.376) and 8.3 METs for the strength training (6*1.376). This gives a total energy expenditure of 750 kCal per session (11*0.5*78 + 8.3*0.5*78).

The physiotherapist registers the attendance of the subjects. The study coordinator will perform several monitoring visits per exercise group.

Previous experience showed that group exercises are preferred in this age group and are better adhered to in the short and long term76(see also Preliminary results). For feasibility reasons, individual home-based exercise is also included.

*Individual Exercise*

The home-based exercise programme comprised Nordic Walking at 75-85% of the maximum heart rate for two times 60 minutes per week. Energy requirements were assumed based on calculated corrected MET’s from Ainsworth.73, 74 It is comparible to study outcomes of Figard-Fabre et al.77 when a higher heart rate of 130/min is assumed for our training programme. For an average woman in our study one 60-minute session of Nordic Walking will comprise an energy expenditure of 515 kCal (6.6*1*78).

Women will receive Nordic Walking poles. Nordic Walking technique will be demonstrated and practised during a group exercise session. To increase the compliance of this individual programme, women will be stimulated to walk with other participants (walking buddy). And supervised group sessions by a sports instructor will be organized. Women have to record the intensity and duration of their weekly Nordic Walk session in an exercise log. Furthermore, women will be asked to wear an activity monitor during the individual exercise sessions: the Actigraph78 ([www.theactigraph.com](http://www.theactigraph.com/)). The physiotherapists will use the Actigraph to check duration, frequency and calorie expenditure of the individual training sessions. For women who do not appreciate Nordic Walking, we will design an alternative programme with the same energy expenditure (e.g. cycling; swimming etc).

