In conclusion, the exerciseprogramme, containing 2 hours of fitness training and 2 hours of Nordic walking, gives a total energy expenditure of 2530 kCal/week (2*750 + 2*515) for a modal participant. Resulting in an average energy expenditure of 360 kCal/day.

Procedures to enhance adherence to the exercise programme are: (1) use of group exercise sessions in combination with a simple individual programme, (2) personal feedback of the physiotherapists, (3) use of exercise logs and an activity monitor (4) stimulate women to find a walking buddy for the individual part, and (5) newsletters.

Diet Intervention

Next to the exercise programme, women enrolled in the combined exercise- plus diet-induced weight loss group will be prescribed an energy-restricted diet creating an extra energy deficit of 250 kcal/day during the weight reduction period of 10-14 weeks. Diet composition and recommendations will be comparable to the baseline diet.

The diet intervention consist of two individual 30 minutes individual sessions with a dietician, 7 telephonic contacts and completion of a food-record. Purpose and content of these contacts are similar as for the diet-group, described in paragraph 3.2.

Participants, whose weekly weight loss does not meet or exceeds the 0.5 kg/week goal for 3 consecutive weeks, will receive extra coaching and/or their programme will be adapted. Participants, who reach the individual weight reduction goal (weight loss of 5-6 kg) before week 14, will enter the weight maintenance period in which energy intake and energy expenditure will be balanced (i.e. they keep exercising but their diet will be adapted).

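### Group E's exercise energy figure (360 kcal/day) is overstated: corrected METs are multiplied by the standard resting rate, and warm-up and cool-down are charged at training rates

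*Protocol*

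**What the plan says.** Section 3.3 builds the exercise energy figure in three steps.

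- **MET correction.** The protocol adapts compendium METs to its population: "Corrected MET’s can be calculated with the use of the Harris-Benedict formula". For the typical participant "we assumed an average weight of 78 kg, length of 1.65 m and age of 58 years". The resulting factor is 1.376, "resulting in MET rates of 11 METs for the aerobic training (8*1.376) and 8.3 METs for the strength training (6*1.376").
- **Session cost.** A group session is half an hour at 11 METs plus half an hour at 8.3 METs, each multiplied by 78 kg, and is stated as 750 kcal. An hour of Nordic Walking is 6.6 METs times 78 kg, stated as 515 kcal. The text says the walking estimate also rests on corrected METs.
- **Weekly total.** The programme "gives a total energy expenditure of 2530 kCal/week (2*750 + 2*515) for a modal participant", averaged to 360 kcal/day. The Summary and the start of the exercise description in Section 3.3 use about 350.

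Table 1 divides a group session into 5-10 min warm-up, 20-25 min endurance, 25 min strength and 5 min cool-down.

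Group D (Section 3.2) is "prescribed a diet creating a mean energy deficit of 500 kcal/day". Group E's diet adds "an extra energy deficit of 250 kcal/day during the weight reduction period of 10-14 weeks" to the exercise. Both arms aim for 5-6 kg at about 0.5 kg per week. The Summary and Sections 1.1, 1.2 and 1.6 describe the weight loss studied in E as driven mainly by exercise.

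**The concern.** A MET corrected for a low resting rate is a multiple of that woman's own resting rate. It should then be multiplied by that lower rate. Section 3.3 multiplies it by body weight alone, which is the standard rate of 1 kcal/kg/h. A lower resting rate thus becomes a higher energy cost of exercise. In addition, the formula charges a full 60 minutes per session at training METs, although Table 1 gives part of that hour to warm-up and cool-down.

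The figure is used in several places:

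- It helps to define arm E.
- It stands behind the description of E's weight loss as mainly exercise-driven.
- Section 3.3 promises women who do not like Nordic Walking an alternative programme of equal energy cost.
- Section 3.3 lets women who reach the goal early offset their exercise expenditure with food.

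An overstated figure carries over into each of these.

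**Working it through.** **Inputs from the protocol.** Section 3.3: 78 kg, 165 cm, 58 years; METs 8 and 6 before correction, 11 and 8.3 after; walking 6.6; two group sessions and two one-hour walks a week; diet deficit 250 kcal/day in E. Table 1: the minutes above. Section 3.2: 500 kcal/day in D.

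**Assumptions.** The coefficients of the revised Harris-Benedict formula for women, 5 kcal per litre of oxygen, and a standard resting rate of 3.5 ml/kg/min. The protocol prints none of these as inputs. However, Section 3.1 uses the adapted formula and cites a re-evaluation of it, and the title of one reference cited for the corrected METs names 3.5 ml/kg/min as the baseline.

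**1. The protocol's figure.**
- Session: 11 × 0.5 × 78 + 8.3 × 0.5 × 78 = 429.0 + 323.7 = 752.7 (stated 750).
- Walk: 6.6 × 1 × 78 = 514.8 (stated 515).
- Week: 2 × 750 + 2 × 515 = 2,530; divided by 7 this is 361 kcal/day (stated 360). The arithmetic reproduces.

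**2. What 1.376 is.**
- Resting rate: 447.593 + 9.247 × 78 + 3.098 × 165 − 4.330 × 58 = 1,429 kcal/day, or 59.5 kcal/h, or 0.76 kcal/kg/h.
- In oxygen: 1,429 / 1,440 / 5 × 1,000 / 78 = 2.544 ml/kg/min.
- 3.5 / 2.544 = 1.376, the protocol's factor to three decimals. The original coefficients give 1.370.

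**3. Consistent units.** Pair each corrected MET with 59.5 kcal/h, or equivalently each uncorrected MET with the standard rate.
- Session: 8 × 0.5 × 78 + 6 × 0.5 × 78 = 546 kcal.
- Walk: (6.6 / 1.376) × 78 = 374 kcal.
- Week: 2 × 546 + 2 × 374 = 1,840 kcal, or 263 kcal/day.
- With the standard rate taken as 1.05 kcal/kg/h (3.5 ml/kg/min at 5 kcal per litre), the daily figure is 276.

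**4. Table 1 minutes at the protocol's own METs.** This step needs no outside coefficient.
- 20 min endurance: (11 × 20/60 + 8.3 × 25/60) × 78 = 556 kcal.
- 25 min endurance: (11 × 25/60 + 8.3 × 25/60) × 78 = 627 kcal.
- Both are lower bounds for the session, because the remaining 10-15 min of warm-up and cool-down are counted as zero.

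**5. Both corrections.**
- Session: 8 × 20/60 × 78 + 6 × 25/60 × 78 = 403 kcal; with 25 min endurance, 455 kcal.
- Day: (2 × 403 + 2 × 374) / 7 = 222 and (2 × 455 + 2 × 374) / 7 = 237 kcal. At 1.05 kcal/kg/h these are 233 and 249.

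**6. Group E's nominal deficit (exercise + 250 kcal/day), against 500 in D.** Figures at 1.05 kcal/kg/h are in brackets.

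| Basis | Exercise, kcal/day | E deficit, kcal/day | Exercise share |
|---|---|---|---|
| As printed | 350-360 | 600-610 | 58-59% |
| MET basis corrected | 263 (276) | 513 (526) | 51% (52%) |
| Table 1 minutes only | 306-326 | 556-576 | 55-57% |
| Both | 222-237 (233-249) | 472-487 (483-499) | 47-49% (48-50%) |

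Section 3.2 equates 500 kcal/day with about 0.5 kg/week. On that conversion 600-610 kcal/day is about 0.6 kg/week, but Section 3.3 states about 0.5.

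**7. Sensitivity.** If the walking figure is left as printed and only the group sessions are put in consistent units, the result is (2 × 546 + 2 × 515) / 7 = 303 kcal/day. E's deficit is then 553 kcal/day and the exercise share 55%.

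**The case against.** **The meaning of 1.376 is inferred.** The coefficients are not printed. But the formula is named, the body size is given, and the revised coefficients return the factor exactly. The inference is strong, though it remains an assumption.

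**The walking figure has separate support.** Section 3.3 calls it comparable with a published study if a higher heart rate is assumed. That is why step 7 is shown; the group-session error remains.

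**Table 1 adds up to about an hour.** It totals 55-65 min, so 60 is not too long, and 30 + 30 can be read as a rounding that folds warm-up into endurance and cool-down into strength. This stands in part. With the whole warm-up at the full endurance rate and cool-down at zero, endurance time is 25-35 min and the session 627-770 kcal, a range that contains 750. The fault is the rate charged for those minutes, not the session length.

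**Little depends on the figure.** Exercise is prescribed by time and heart rate, and neither the sample size nor the analysis uses the energy estimate. This stands and limits the weight of the point.

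**A stronger reading.** A reader might infer from 500 against about 600 kcal/day that the prescriptions contradict the objective of equal weight loss, so that E would lose more weight and the hormone contrast would be biased. The protocol does not support that. Both arms share the 5-6 kg goal. Both are coached or adapted when loss falls short of or exceeds 0.5 kg/week for three weeks. Both move to maintenance once the goal is reached. Correcting the exercise figure also removes most of the gap.

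**Conclusion.** The point holds as an error in a stated figure. The 750 kcal per session, 2,530 kcal/week and 350-360 kcal/day are overstated. With the MET basis corrected, the daily figure is about 263-276 kcal, so the printed value is about 1.31 to 1.38 times too high. With Table 1 minutes as well, it is about 222-249, a lower bound because warm-up and cool-down are left out. The size of the MET error rests on the assumed coefficients and on the walking value being a corrected MET, as the text says.

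As printed, the nominal deficits of 600-610 in E and 500 in D do not both fit one pace of about 0.5 kg/week. Corrected, E's is about 470-526, close to D's, and exercise provides about 47-52% of it. That is roughly half, which bears on the description of E's weight loss as mainly exercise-driven.

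A reader might also infer that Section 7.2 lacks a rule for judging whether weight loss was equal. This is not a finding. Weight is already a secondary endpoint, Section 7.2 compares hormone effects before and after adjustment for change in body fat, and further detail may sit in an analysis plan that is not shown.

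**What to change.** In Section 3.3, state the formula and resting rate behind 1.376, then recompute the session, weekly and daily figures with each MET value paired with its own resting rate. Use the Table 1 minutes, with an explicit rate for warm-up and cool-down. Carry the result to the opening of the exercise description and to the Summary.

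Then reconcile the passages giving 350/360, 250 and 500 kcal/day with the common pace of about 0.5 kg/week and with the wording that calls E's weight loss mainly exercise-driven. Which prescription is right is for the sponsor and investigators; none is proposed here.

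Use the corrected figure wherever the protocol relies on it: alternative programmes matched on energy cost, and intake compensation for women who reach the goal early.

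The cost is a short recalculation and a few edited sentences. Sample size and analysis stay as they are. The downside is that the stated exercise share becomes less favourable to the trial's description of arm E.

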## Waiting list control group (group C)

Participants in the waiting list control are requested to retain body weight according to the isocaloric diet and to maintain their habitual exercise pattern. We will give very clear recommendations on this throughout the study. Potential changes in weight, exercise and eating pattern will be monitored by four phone calls by the researchers or dietician (See figure 1). After completion of the 5 month study period, the control participants will be provided with all study materials of the diet and exercise programme. Additionally, we will offer them four dietary weight loss group sessions and three exercise group sessions (including one exercise education session).

**Figure 1: Time Schedule**

|  | *Run-in* | | | | | | *Intervention* | | | | | | | | | | | | | | *Maintenance** | |
| --- | --- | --- | --- | --- | --- | --- | --- | --- | --- | --- | --- | --- | --- | --- | --- | --- | --- | --- | --- | --- | --- | --- |
| *Week* | 0 | 1 | 2 | 3 | 4 | 5 | 6 | 7 | 8 | 9 | 10 | 11 | 12 | 13 | 14 | 15 | 16 | 17 | 18 | 19 | 20 | 21 |
| **DIETARY COUNCELLING** |  |  |  |  |  |  |  |  |  |  |  |  |  |  |  |  |  |  |  |  |  |  |
| Face to face instruction baseline diet | **X** |  |  |  |  |  |  |  |  |  |  |  |  |  |  |  |  |  |  |  |  |  |
| Face to face instruction energy restricted diet |  |  |  |  |  |  | **DE** |  |  |  |  |  |  |  |  |  |  |  |  |  |  |  |
| Face to face instruction maintenance diet |  |  |  |  |  |  |  |  |  |  |  |  |  |  |  |  | **---------- DE ---------** | | | |  |  |
| Group sessions for education and motivation |  |  |  |  |  |  |  | **D** |  | **D** |  | **D** |  |  |  | **D** |  |  |  | **D** |  |  |
| Individual monitoring, motivation and education by telephone |  |  | **X** |  | **X** |  | **C** |  | **DE** |  | **X** |  | **DE** |  | **DE** |  | **DE** |  | **DE** |  | **X** |  |
| **DIETARY MEASUREMENT** |  |  |  |  |  |  |  |  |  |  |  |  |  |  |  |  |  |  |  |  |  |  |
| Dietary history intake interview | **X** |  |  |  |  |  |  |  |  |  |  |  |  |  |  |  |  |  |  |  |  |  |
| 3-consecutive-day food-record |  |  | **X** |  |  |  |  |  |  | **X** |  |  |  |  |  |  |  |  |  |  | **X** |  |
| **OTHER MEASUREMENTS** |  |  |  |  |  |  |  |  |  |  |  |  |  |  |  |  |  |  |  |  |  |  |
| Weight self-monitoring | **X** | **X** | **X** | **X** | **X** | **X** | **DE** | **DE** | **DE** | **DE** | **X** | **DE** | **DE** | **DE** | **DE** | **DE** | **DE** | **DE** | **DE** | **DE** | **X** | **X** |
| Measurements e.g MRI, blood |  |  |  |  |  | **X** |  |  |  |  |  |  |  |  |  |  |  |  |  |  |  | **X** |

**X= all study groups**

**D = Diet-induced weight loss group only**

**DE = Diet-induced weight loss group and combined Exercise- plus diet-induced weight loss group**

**C= Control group**

* The weight maintenance period starts from week 10 as soon as the weight reduction goal of 5-6 kg is obtained, and at least in week 19.

# STUDY POPULATION

## Population (base)

Women will be recruited through a random selection out of the female population aging 50-69 years in the surroundings of Utrecht and Enschede. For their contact details, we will use the community register (GBA) of Utrecht and Enschede and the UMCU register with potential candidates for scientific research (POKA).

It is likely that enough women can be recruited from this random selection since this age group is mainly postmenopausal and in the Netherlands 55% of these women is overweight 79. Furthermore the participants will be recruited in two separate areas which will enlarge the number of possible candidates.

## Inclusion criteria

- Female

- 50-69 years of age

- Postmenopausal (>12 months after last menses)

- BMI 25-35 kg/m2

- Sedentary (<2 hours per week of at least moderately intensive activities (>4 MET))

- Willing to be randomly assigned to one of the three study arms

- Informed consent to participate in all screening and study activities.

## Exclusion criteria

- Presently using sex-hormones

- Maintenance use of corticosteroids

- Suffering breast cancer (or in medical history).

- Suffering other types of cancer now or in the past 5 years, except for non-melanoma skin cancers

- Suffering diabetes mellitus (type 1 and 2) or other endocrine related diseases

- Smoking

- Alcohol or drug abuse

- Any disorder that might impede participation in the exercise programme

- Following, or the intention to follow, a structured weight loss programme elsewhere

- In the investigator’s opinion, subject lacks the ability or motivation to fulfil the study programme completely and/or successfully in either one of the three arms

## Sample size calculation

Sample size calculations are based on the effect of the interventions on serum estradiol levels. The following comparisons will be made:

1) diet-induced weight loss versus combined exercise- plus diet-induced weight loss

2) diet-induced weight loss versus control

3) combined exercise- plus diet-induced weight loss versus control

The following assumptions are based on the results of the SHAPE study in women with a BMI≥25, the DIANA trial46 and the studies of McTiernan13 and Friedenreich 15:

- Mean log-transformed serum estradiol levels: 2.28 pg/ml
- Log-transformed SD: 0.44 pg/ml
- Change in diet group: -12%; pg/ml
- Change in exercise-weight loss group: -20%: pg/ml
- Power: minimally 80%
- Level of significance: 0.05 for comparison 1 and 0.025 for comparisons 2 and 3 (taking into account multiple testing).
- Drop-out: 5% in all groups
- Non-compliance/contamination: 15%

First, we calculated the sample size for the first comparison, i.e. diet-induced weight loss (n=85) versus exercise-induced weight loss (n=85), since the difference in estradiol levels between these groups is expected to be the smallest (8%). Furthermore, we think a difference of 8% will be of clinical relevance. Based on the estimated sample sizes, we calculated the number of subjects needed in the control group (n=36). The sample size of the control group can be much smaller, since the expected difference with the interventions groups is large (12% and 20%, respectively).

The sample size calculations resulted in the following estimated numbers per group, taking into account drop out and non-compliance:

- - Control group: 45
  - Diet group: 104
  - Combined exercise plus diet group: 104

The accompanying power for the other hormones to demonstrate an 8% difference between the diet and exercise group for is tabulated below:

|  | Diet vs. exercise |
| --- | --- |
| Estrone | 83% |
| Testosterone | 100% |
| SHBG | 96% |

*Abdominal fat measured by MRI*

Based on the study of Ross et al.80 (in their obese study population: mean total visceral fat was 2.3 kg SD 0.8 kg), we calculated that 81 subjects are needed to demonstrate a difference of 0.2 kg visceral fat (Alpha=0.05; Beta=0.20.) between the diet and exercise group.

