The second intervention study was done by our group. In the SHAPE study, we assessed the effect of a moderate-to-vigorous intense exercise programme on sex hormone levels in 189 postmenopausal sedentary women (KWFno: UU 2003-2793)14.We also did not find an overall intervention effect on sex hormone levels, but again in women who lost >2% body fat androgen levels (testosterone and androstenedione) were on average, lower in the intervention group compared to the control group (8% and 10%, respectively).

The third trial (ALPHA trial (Alberta Physical Activity and Breast Cancer Prevention Trial)) assessed a year-long aerobic exercise trial among 320 postmenopausal Canadian women. This study resulted in significant reductions in estradiol and free estradiol by 13% compared with reductions of 3% and 4% in the control group, respectively. Additionally, SHBG levels increased significantly in the intervention group compared to controls. Adjustment for weight change during the study attenuated the effect on SHBG but not on (free) estradiol levels. The difference in overall effect between the studies might be caused by the effects of the intervention on weight change: -1.4 kg in McTiernan study, -0.5 kg in SHAPE trial and -2.3 in the ALPHA trial. On the other hand, the ALPHA study suggests an effect of exercise on estradiol independent of changes in adiposity by analysing the intervention effect after adjustment for weight change.

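### Section 4.4 appears to apply the 12% and 20% falls to the mean of the log values, so its 80% power for an 8% estradiol difference does not follow from its own inputs

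*Protocol*

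**What the plan says.** Protocol section 4.4 (Sample size calculation) bases the trial size on serum estradiol. Its inputs are "Mean log-transformed serum estradiol levels: 2.28 pg/ml", "Log-transformed SD: 0.44 pg/ml", "Change in diet group: -12%; pg/ml" and "Change in exercise-weight loss group: -20%: pg/ml". Power is to be at least 80%, with a significance level of 0.05 for D versus E and 0.025 for each comparison with control.

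The D-versus-E contrast is sized first, at 85 per arm, as the smallest expected difference. The protocol adds that "we think a difference of 8% will be of clinical relevance". The control arm is then set at 36. After allowance for drop-out and non-compliance the numbers become 104, 104 and 45. A short table gives power for the other hormones, introduced by "The accompanying power for the other hormones to demonstrate an 8% difference between the diet and exercise group for is tabulated below".

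Section 7.2 (Analysis) takes changes in the hormones as endpoints, analyses them by linear regression, and uses log transformation where the distribution is not normal.

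**The concern.** The percentages are drawn from earlier trials, which section 1.4 reports as changes in concentration. For example: "This study resulted in significant reductions in estradiol and free estradiol by 13% compared with reductions of 3% and 4% in the control group". On the log scale a percentage change in concentration is an additive shift: a 12% fall is ln 0.88, whatever the mean. Section 4.4 instead lists a log mean among its inputs. A correct calculation on the log scale does not need one.

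Taking a percentage of a log mean has no fixed meaning, because the log mean moves with the unit. Expressed per decilitre, the same data would have a log mean of 2.28 + ln 100 = 6.89 and an unchanged SD. Then 8% of the log mean would be 0.55 instead of 0.18, and the required sample size would collapse although nothing about the women had changed.

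D versus E tests the hypothesis in section 1.2, that weight loss driven mainly by exercise lowers estradiol more than equivalent loss by diet alone. If power for a difference the protocol calls clinically relevant is well below the stated figure, an inconclusive result on this contrast would be given more weight than it can bear. The small control arm rests on the same calculation.

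**Working it through.** **Inputs (section 4.4).** Log mean 2.28; log SD 0.44; falls of 12% and 20%; power 80%; alpha 0.05 (D vs E) and 0.025 (versus control). Natural logs and two-sided tests are assumed, since the protocol states neither. The normal approximation is used throughout.

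**1. Reproduce the 85.** Apply the percentages to the log mean and round the arm means to two decimals:
- D: 2.28 × 0.88 = 2.01
- E: 2.28 × 0.80 = 1.82
- difference 0.19

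n per arm = 2 (1.960 + 0.842)² × 0.44² / 0.19² = 84.2, so **85**, as stated. Without rounding, the difference is 0.08 × 2.28 = 0.1824 and n = 91.3, so 92.

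**2. Reproduce the 36.** By the same step, control minus diet is 2.28 − 2.01 = 0.27. Power = Φ(0.27 / [0.44 √(1/85 + 1/n)] − 2.241). This gives 79.2% at n = 35 and 80.1% at n = 36, so **36** is the smallest control arm reaching 80%, as stated.

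**3. Other ways to express the effect.** None of these gives 85 per arm with SD 0.44:

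| Log difference, D vs E | n per arm |
|---|---|
| ln(0.88/0.80) = 0.0953 | 335 |
| −ln 0.92 = 0.0834 | 438 |
| 0.08 absolute | 475 |

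**4. What the calculation assumes in concentration terms.**
- D: 1 − exp(−0.27) = 24% fall, not 12%
- E: 1 − exp(−0.46) = 37% fall, not 20%
- E relative to D: 1 − exp(−0.19) = 17% lower

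The stated 12% versus 20% is a ratio of 0.80/0.88 = 0.909, or 9% lower.

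**5. Power at 85/85/36 for the stated falls, SD 0.44, no baseline adjustment.** Power = Φ(δ / [0.44 √(1/n₁ + 1/n₂)] − z).

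| Comparison | δ | alpha | Power |
|---|---|---|---|
| E vs D | 0.0953 | 0.05 | 29% |
| D vs C | −ln 0.88 = 0.1278 | 0.025 | 22% |
| E vs C | −ln 0.80 = 0.2231 | 0.025 | 62% |

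If the 8% is read as a ratio of exactly 0.92, E vs D power is 23%.

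**6. Credit for baseline adjustment.** Residual SD = 0.44 √(1 − r²), where r is the correlation between baseline and end-of-study log estradiol. The protocol gives no r, so these values are assumptions:

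| r | E vs D power |
|---|---|
| 0.5 | 37% |
| 0.7 | 51% |
| 0.8 | 65% |
| 0.85 | 76% |

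For 80% power the residual SD must be 0.0953 / (2.802 × √(2/85)) = 0.222, so r = √(1 − (0.222/0.44)²), about 0.86. For D vs C the same calculation gives about 0.88. An analysis of change scores without baseline as a covariate has SD 0.44 √(2(1 − r)) and does less well: 29% at r = 0.5 and 45% at r = 0.7.

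**7. Detectable E-versus-D difference at 85 per arm, 80% power.** Unadjusted: 2.802 × 0.44 × √(2/85) = 0.189, or 17% lower. At r = 0.7 the SD is 0.314, giving 0.135, or about 13% lower.

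**The case against.** The step is inferred: section 4.4 does not say how the percentages were put on the log scale, and the match at 85 needs arm means rounded to two decimals. The best innocent account is that the correct log ratio was used with an unstated residual SD of about 0.22, which does give 85 per arm. But that SD then requires about 44 controls (36 would give 74% power), and the protocol lists 0.44. Applying the percentages to the log mean gives both 85 and 36 from the listed inputs, so the inference stands, as an inference.

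A reader might conclude that the trial simply has 29% power and needs 335 women per arm. The protocol does not support that flat statement. Both figures assume end-of-study levels compared without baseline information, whereas section 7.2 plans to analyse changes. True power depends on a correlation that is not given. This objection stands, and the power must be given as a range.

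A reader might also infer that the estrone, testosterone and SHBG powers contain the same error. That cannot be tested, because no means or SDs are given for those hormones.

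Finally, type I error, the effect estimates and their confidence intervals are untouched, and no section plans to read a null result as proof of no effect. That also stands: the defect lies in the stated sizing and power.

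**Conclusion.** The point holds. On the protocol's listed inputs, 85/85/36 does not deliver at least 80% power for falls of 12% versus 20%. The sizes correspond to estradiol about 17% lower in E than in D, where the stated assumptions imply about 9%. E-versus-D power is about 29% without baseline adjustment and 37% to 76% for r from 0.5 to 0.85. The claim would be rescued only by r of about 0.86 or more for E vs D and about 0.88 for D vs C.

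This rests on natural logs, two-sided tests and 0.44 being the SD of log levels, as its listing beside the log mean suggests. Base-10 logs would imply a geometric mean of about 190 pg/ml and lower E-versus-D power, about 9%.

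**What to change.** Redo section 4.4 with the effects as log ratios (ln 0.88 and ln 0.80) and a residual SD that matches the planned analysis, with its source. If baseline adjustment is credited, state r; the sponsor's earlier exercise trial, already cited as a source of the assumptions, is the natural place to estimate it.

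Then, for all three comparisons, restate either the true power or the detectable ratio at the evaluable numbers 85/85/36. For E vs D the detectable difference is about 17% lower unadjusted and about 13% lower at r = 0.7. The recruited numbers 104/104/45 should not be used for this, since they already contain the allowance for drop-out and non-compliance.

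State the means and SDs behind the estrone, testosterone and SHBG powers, and recompute them on the log-ratio scale if they used the same step.

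The cost is about half a day of recalculation and a text amendment. No extra recruitment is needed; the downside is a less favourable stated power.
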